**Table 1: Site Selection**

| Site              | Number of ICUs | Number of Wards | Total Number of Units/Wards | VISN 23 | Aim 2 |
|-------------------|----------------|-----------------|-----------------------------|---------|-------|
| Ann Arbor VA      | 2              | 4               | 6                           |         |       |
| Baltimore VA      | 3              | 2               | 5                           |         | X     |
| Boston VA         | 3              | 8               | 11                          |         |       |
| Iowa City VA      | 1              | 2               | 3                           | X       | X     |
| Miami VA          | 3              | 3               | 6                           |         | X     |
| Minneapolis VA    | 2              | 7               | 9                           | X       | X     |
| Omaha VA          | 1              | 2               | 3                           | X       | X     |
| Portland VA       | 1              | 2               | 3                           |         | X     |
| San Antonio VA    | 3              | 5               | 8                           |         |       |
| Salt Lake City VA | 2              | 3               | 5                           |         |       |
| Total             | 21             | 38              | 59                          |         |       |

**Aim 1** involves a sequential cluster-randomized controlled trial that will be conducted in 10 VA hospitals to evaluate the individual and combined impact of three approaches to improving hand hygiene compliance. The primary outcome measure will be directly observed hand hygiene. The unit of analysis will be hospital wards/ICUs.

**Outcome Measures:** Hand hygiene compliance is the primary outcome measure. Compliance rates will be determined using the same methods of direct observation of HCWs developed by [name] for his VA HSR&D funded study (IIR 09-099). (See Cluster Randomized Trials (CRT) in 2.A.) The secondary outcome measure is MRSA acquisition. Both compliance and MRSA infection rates will be collected monthly throughout the project for each of the 59 units.

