*Operationalization of Primary Outcome:* Nurses, physicians and other staff will be observed for 10 consecutive minutes of clinical activity on the study wards and ICUs. Observers will be research staff specifically trained and validated in hand hygiene observations. (See Appendix for standardized observation worksheet.) The observation periods will be 10 minutes long so that observers can be transiently on the wards/units without their presence being noticed, which should minimize the Hawthorne effect. As [name] has done in his previous study, the observers will be given a "cover story" so that the true purpose of their observations will be hidden. Therefore, while observers will be on the wards, the HCWs will not know they are being watched for infection control purposes, so they will not artificially increase their compliance. In ICU settings, we will state that the observers are collecting data for a severity of illness aggregate measure, such as the APACHE score. In non-ICU, medical/surgical ward settings the observer will state that they are doing a patient movement and activity of daily living survey to determine the proportion of time patients who are isolated or non-isolated receive their trays of food or are transported outside of their rooms to physical therapy or radiology, etc. The standardized observation instructions and training protocol has been successfully implemented in other studies by the team. Hand hygiene opportunities at entry and exit of a patient's room will be recorded. We are using entry and exit because it is the one of the most common "hand hygiene opportunities" reported in the literature and by VA facilities. However, we will also record observations of the 5 Moments of Hand Hygiene as current hand hygiene observation guidelines recommend. Observations will occur during the day shift (75%) and night shift (25%). In addition, observations will include weekends (20%) and weekdays (80%).

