dependent variable in each model will be the monthly hand hygiene compliance rate. The numerator will be the number of times a HCW disinfects their hands while the denominator will be the number of opportunities for hand hygiene. The ideal denominator is the WHO 5 Moments of Hand Hygiene and where possible, we will collect these data. However, our current IIR 09-099 suggests that the most reliably measurable moments are room entry and room exit. Separate models will be run for the WHO 5 moments (combined as one dichotomous measure and for each of the individual “moments”), room entry compliance, and room exit compliance. Independent variables will include the tested intervention, the bed size and type of unit, monthly census, estimated monthly nurse to patient ratios, and other known confounders associated with hand hygiene compliance. The results will advance understanding of the effectiveness of individual interventions and their combined effectiveness as a bundle.

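### No lead measure is fixed for the primary outcome: eight compliance models are planned, none is primary or pools room entry with exit, and the carry-forward rules and power table name no rate

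*Protocol*

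**What the plan says.** **Section 5.1, Outcome Measures:** "Hand hygiene compliance is the primary outcome measure". No moment or denominator is attached.

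**Section 5.1, Operationalization of Primary Outcome:** "Hand hygiene opportunities at entry and exit of a patient's room will be recorded". The reason given begins "We are using entry and exit because it is the one of the most common" kinds of opportunity reported. The 5 Moments come as an addition: "However, we will also record observations of the 5 Moments of Hand Hygiene as current hand hygiene observation guidelines recommend".

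**Section 5.6, Aim 1, Analysis:** "The ideal denominator is the WHO 5 Moments of Hand Hygiene", to be collected where this is possible. The text then says that experience in the team's current study suggests "the most reliably measurable moments are room entry and room exit". It commits to the following: "Separate models will be run for the WHO 5 moments (combined as one dichotomous measure and for each of the individual" ones). Two further models complete the list: "room entry compliance, and room exit compliance".

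**Section 5.1, Study Procedure:** units are ranked on baseline compliance and randomised in blocks of three for Phase 2. Phase 4 assignment is stratified on Phase 3 compliance. The Phase 2 sign strategy with the highest compliance goes to all 59 units in Phase 3. The Phase 4 intervention with the highest rates goes to all hospitals in Phase 5, unless the two do equally well. None of these rules says which rate is meant.

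**Section 5.6, Power Calculation and Table 2:** baseline rates of 60%, 65% and 70% for Phases 2, 4 and 6, a 5-point increase, 30,000 observations per group and 99% power. The rate is described only as the primary outcome.

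**The concern.** A single primary outcome needs a single number per unit-month. Section 5.1 points to entry and exit taken together. Section 5.6 has no model for that quantity: entry and exit are modelled apart, and a different denominator is called ideal. So the stated analysis contains no model that matches the operational primary outcome.

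Two things are at stake. First, if the significance claim can rest on whichever model is favourable, the nominal error rate for the primary outcome no longer applies. Second, the protocol uses the undefined rate during the trial. It determines the blocks, the sign frequency that every unit receives from Phase 3, and the add-on that hospitals receive from Phase 5. In the Gantt chart, Phase 3 (months 19-21) starts directly after Phase 2 (months 13-18), so the choice is made on data just seen and shapes everything after it.

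**Working it through.** **1. The plan's own power figure.** Inputs from section 5.6: n = 30,000 per group and a 5-point increase. Assumptions: two-sided 5% level (the protocol states none) and independent observations. Formula: power = Φ(0.05/SE − 1.96), with SE = √[(p₁(1−p₁) + p₂(1−p₂))/30,000].

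| Phase | Rates | SE | 0.05/SE | Power |
|---|---|---|---|---|
| 2 | 60% to 65% | √(0.4675/30,000) = 0.00395 | 12.7 | >99.9% |
| 4 | 65% to 70% | √(0.4375/30,000) = 0.00382 | 13.1 | >99.9% |
| 6 | 70% to 75% | √(0.3975/30,000) = 0.00364 | 13.7 | >99.9% |

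The stated 99% reproduces on these terms. (Clustering is a separate matter, not taken up here.)

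**2. Which rate is in Table 2?** Preliminary Studies reports 32.9% on entry and 50.8% on exit. Any pooled rate lies between them; with equal numbers it is (32.9 + 50.8)/2 = 41.9%. Pilot baselines were 34% and 38.8% on entry, and 52.5% and 56.4% on exit. No observed baseline for entry, exit or a mix of them reaches 60%. The 60% may be a projection with signs already displayed, since all Phase 2 arms have signs, but the text does not say so.

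**3. Model count.** 5 Moments combined (1) + each moment (5) + entry (1) + exit (1) = 8.

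**4. False-positive risk per contrast, if any one model could support the claim at 5%.**
- Entry and exit only, independent: 1 − 0.95² = 0.0975, about 10%.
- All eight, independent: 1 − 0.95⁸ = 0.337. Independence cannot hold here, because one measure is a composite of five others.
- All eight, equal pairwise correlation, by simulation of normal test statistics: 30% at 0.3, 25% at 0.5, 19% at 0.7 and 12% at 0.9.
- All eight, structured overlap: the composite is the sum of the five moments, entry has correlation 0.7 with one moment, and exit has correlation 0.7 with the sum of two others. The result is 29%, 26%, 23% and 20% when the correlation among the moments is 0, 0.3, 0.5 and 0.7.
- One designated measure: 5%.

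The correlations are assumptions; the protocol gives none.

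**5. Does the measure matter in the team's own data?** In the pilot, the gain-framed, patient-focused sign had 53% against 29% on entry (p = 0.042) and 79% against 52% on exit (p = 0.36). It ranked first on both, but only entry reached 5%. The significance conclusion depended on the measure; the ranking did not.

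**6. Would simple pooling be enough?** At 32.9% and 50.8%, suppose that the share of entry observations is 60% in one unit and 40% in another (assumed shares). The pooled rates are 0.6 × 32.9 + 0.4 × 50.8 = 40.1% and 0.4 × 32.9 + 0.6 × 50.8 = 43.6%. That is a gap of 0.2 × 17.9 = 3.6 points with identical behaviour, against a target effect of 5 points. A pooled measure therefore has to handle the mix.

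**The case against.** The best defence is that section 5.1 does lean to entry and exit. It says these are being used and gives a reason, and the 5 Moments are recorded as well. Section 5.6 can be read the same way, with one denominator as the ideal and the other as the workable choice. That stands, and it narrows the ambiguity to mainly entry, exit or pooled. It does not remove it, because section 5.6 models entry and exit separately and ranks neither.

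A second defence is that ranking of models and multiplicity adjustment commonly sit in a statistical analysis plan, which is not shown. That also stands: a missing multiplicity rule alone would not be a finding. The identity of the measure is different, because the protocol's own blocking and carry-forward rules need it.

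Three stronger readings are tempting and are not supported:
- A reader might infer that any of the eight results may be claimed, giving a 34% error rate. The protocol does not say that one significant model is enough, and 34% is only the independence figure.
- A reader might infer from the 18-point gap between entry and exit that they would favour different arms. A difference in level says nothing about ranking, and in the pilot the same sign led on both.
- A reader might infer that the 5 Moments form a denominator selected by what is visible and differing by unit. The text says only that they are collected where possible.

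**Conclusion.** The concern holds in this form: one primary outcome is named, it is operationalised mainly as entry and exit, and none of the eight planned models is designated primary or matches that definition. The blocking, the Phase 3 and Phase 5 selection rules and Table 2 share the gap.

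If any model could support the claim at an assumed two-sided 5% level, the risk per contrast is up to about 10% for entry and exit alone, and roughly 12% to 30% across all eight under plausible positive correlation. These figures concern the significance claim only. The carry-forward rule picks the highest rate, not a significant one, so they do not measure the risk of choosing a wrong arm, and nothing in the document shows that such a reversal would occur. The data remain usable. What is missing is a primary test and a selection path fixed in advance.

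**What to change.** Designate one primary measure in section 5.1 and repeat it in section 5.6. An example is pooled room-entry and room-exit compliance per unit-month, which follows the operational definition and the protocol's own statement on reliability. Include an entry/exit term in the model, or standardise to a fixed mix, so that the mix does not drive the result. Naming entry alone or exit alone would also close the gap.

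Use that same measure for:
- the primary test in each phase
- the Phase 2 blocking and Phase 4 stratification
- the Phase 3 and Phase 5 selection rules, including the clause for equal efficacy
- Table 2, with the source of the 60%, 65% and 70% stated

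Label the separate entry and exit models and all 5 Moments models as secondary. The wording should be settled before the Phase 2 randomisation, because the blocks depend on it.

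The cost is protocol wording and a restated power table, with no new data collection. The small downside is that a pooled measure may hide a difference between entry and exit effects; the secondary models will show it.

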#### AIM 2:

Analysis: After the initial site visits, the study team will review transcripts and conduct an initial thematic content analysis. Drs. [name], [name] and [name] will read a subset of transcripts and generate a preliminary codebook through a series of meetings. The thematic codes will include *a priori* codes such as hand hygiene compliance data collection, hand hygiene interventions, facilitators and barriers to hand hygiene compliance, as well as inductive codes which are likely to emerge during data collection. The codebook will consist of top-level thematic codes, which will be used to “tag” textual data with the main themes. The codebook will then be tested against subsequent interviews.

To test the codebook, [name] and the coding team will code one IC team member interview and one staff focus group and enter coding in MAXQDA10 individually. We will then meet together to review results. MAXQDA10 allows for side-by-side comparison of coding and a measure of agreement. We will systematically compare coding and discuss coding until consensus is reached. Final consensus will be entered in MAXQDA10. If measure of agreement is 80% or higher between coders, the coding team will divide the transcripts and will continue to code the remainder of the focus groups and interviews, periodically coding the same transcript to test whether agreement continues at the 80% level. If the agreement is not 80% for all codes, [name] will continue to work with the team and revisions to the codebook will be discussed. The process will be repeated until 80% agreement is reached. At least 10% of the transcripts will be consensus coded during the coding period.

During Phases 2-6, the qualitative team will continue to apply the codebook to the newly conducted interviews, but it is likely the codebook will expand to include specific codes about the study interventions. The coding team will continue to test agreement as the codebook is revised.

In the final Phase, the coding team will code the transcripts from the post-intervention site visits. The analysis will assist in writing a second case study of each hospital. The revised case studies will highlight changes in the “hand hygiene culture”. It will also be used to develop a report on the facilitators and barriers to the interventions within the context of the intervention

sites. This report will be disseminated with the intervention results to improve implementation of the final hand hygiene bundle.

After top-level coding is complete, the research team will discuss which codes warrant more detailed subcoding. Our team has followed Miles and Huberman's approach to subcoding, called matrix analysis, in several projects. In matrix coding, we develop a list of subcodes under a top-level theme and then code both for the presence or absence of the subcode, as well as content. MAXQDA10 has several features which aid in this level of analysis, including hierarchical coding, weighting of coded segments, and multi-factor queries in matrices. This coding will provide more detailed analysis on specific issues the research team finds most relevant and will primarily be used in the development of manuscripts for peer-reviewed publications.

### Project Gantt Chart

|                                                                                    | Qualitative
Evaluation
1-6 | Phase1
Months
7-12 | Phase 2
Months
13-18                                                                                            | Phase 3
Months 19-21                                             | Phase 4
Months
22-27                                                                                                     | Phase 5
Months
28-30                    | Phase 6
Months
31-36                                                                                                                       | Qualitative
Evaluation
37-42 |
|------------------------------------------------------------------------------------|----------------------------------|--------------------------|-----------------------------------------------------------------------------------------------------------------------|---------------------------------------------------------------------|--------------------------------------------------------------------------------------------------------------------------------|-----------------------------------------------|--------------------------------------------------------------------------------------------------------------------------------------------------|------------------------------------|
| HH
Observations                                                                 |                                  |                          |                                                                                                                       |                                                                     |                                                                                                                                |                                               |                                                                                                                                                  |                                    |
| Aim 1                                                                       |                                  |                          |                                                                                                                       |                                                                     |                                                                                                                                |                                               |                                                                                                                                                  |                                    |
| Randomization                                                                      |                                  |                          | -Control:
no change
in signs
-Arm 1:
signs
changed
monthly
-Arm 2:
signs
changed
weekly | -Implementation
of most
effective sign
change
frequency | -Control:
Signs only
-Arm C:
Signs and
pocket
hand
sanitizer
-Arm D:
Signs and
HCW hand
cultures | -Arm C
only
OR
-Arm D
only | -Arm C
only
OR
-Arm D
only
AND
-Arm E:
Signs,
pocket
hand
sanitizers,
and HCW
hand
cultures |                                    |
| Analysis                                                                           |                                  |                          |                                                                                                                       |                                                                     |                                                                                                                                |                                               |                                                                                                                                                  |                                    |
| Aim 2                                                                       |                                  |                          |                                                                                                                       |                                                                     |                                                                                                                                |                                               |                                                                                                                                                  |                                    |
| Site Visits                                                                        |                                  |                          |                                                                                                                       |                                                                     |                                                                                                                                |                                               |                                                                                                                                                  |                                    |
| Semi-
structured
interviews                                                  |                                  |                          |                                                                                                                       |                                                                     |                                                                                                                                |                                               |                                                                                                                                                  |                                    |
| Analysis                                                                           |                                  |                          |                                                                                                                       |                                                                     |                                                                                                                                |                                               |                                                                                                                                                  |                                    |
| Dissemination and Implementation                                            |                                  |                          |                                                                                                                       |                                                                     |                                                                                                                                |                                               |                                                                                                                                                  |                                    |
| Quarterly
Advisory Panel
Meetings                                            |                                  |                          |                                                                                                                       |                                                                     |                                                                                                                                |                                               |                                                                                                                                                  |                                    |
| Annual
Meetings with
CREATE
Dissemination/
Implementation
Committee |                                  |                          |                                                                                                                       |                                                                     |                                                                                                                                |                                               |                                                                                                                                                  |                                    |
| Submit
manuscripts to                                                           |                                  |                          |                                                                                                                       |                                                                     |                                                                                                                                |                                               |                                                                                                                                                  |                                    |

|                           |  |  |  |  |  |  |  |  |
|---------------------------|--|--|--|--|--|--|--|--|
| peer-reviewed
journals |  |  |  |  |  |  |  |  |
|---------------------------|--|--|--|--|--|--|--|--|

1170

